### Eligibility determination and retention

Young adults (age 18–24) will be screened for study inclusion criteria (meeting criteria for psychological distress on Kessler-6 [49] or self-reported prior diagnosis of depression, anxiety, bipolar or a psychotic disorder) and invited to participate at the point of assignment to a TH/RRH program. Young adults will be told of the opportunity to participate in the study at the time of intake to a program and asked for permission to provide their names to the study team if interested. When the young adult meets the centralized housing criteria that qualifies them for TH/RRH, they are referred to a receiving agency who will provide names to the study team. The team will screen for eligibility and schedule a baseline interview. Trained graduate-level research assistants from the study team will obtain informed consent and administer the survey in person or via phone or Zoom. In order to track outcomes through the course of the 6-month intervention, we will administer surveys at baseline, the midpoint (3 months), end of the intervention (6 months) and follow-up 6 months later (12 months). We will also conduct qualitative interviews with all young adults in the first phase of the feasibility pilot (*n* = 8) and each of the professionals involved in implementing it (*n* = 5) to explore qualitatively assess implementation outcomes of acceptability and appropriateness. Interviewers will contact all young adults in both conditions of the trial monthly to maintain contact and increase retention. At the time of enrollment, a locator form will be completed to gather detailed data about contact information including social media contacts and the names of others who may know how to contact the young adult. Participants’ incentives for completing study interviews increase over time with the aim of increasing retention.

### Setting and location

This study will take place in Harris County, TX, which contains the city of Houston. In Fall 2021, the community was awarded 10 million dollars through a Youth Homelessness Demonstration Project (YHDP) Grant from Housing and Urban Development (HUD) which funded three TH/RRH providers in the county. Entry into the homelessness system is managed through a coordinated access system with a consistent assessment process and centralized wait list, which is prioritized based on a screener that asks respondents to self-report whether they have been diagnosed with a mental disorder. For the first phase of this study, we will partner with one community agency that runs a TH/RRH program and has on-site housing provided by the agency. We plan to potentially expand to include two other community agencies that also provide TH/RRH for the second phase of the pilot, where we randomize young adults to either receive the intervention or housing supports as usual. These agencies provide both scattered site housing as well as on-site housing. TH/RRH is a newer housing model that HUD approved for funding in 2017. It is specifically designed for young adults to allow them to spend some time in a more structured setting (transitional housing) prior to transitioning to their own apartment in rapid rehousing (RRH) where they are expected to pay a portion of their rent. The programs are offered together but allow young adults some flexibility in whether they desire to start in TH or go directly to RRH, and also whether they desire to transition to RRH as the plan after TH. The community setting for this study is in a learning phase for offering this combination of housing, so expanding to three sites could allow us to examine the feasibility of *Charge Up!* across multiple agencies who may be managing the program in somewhat different ways.

### Description of the Charge Up! intervention

Based on the results of our preliminary work, we identified three roles that we have incorporated into the drafted manuals for refinement (summarized in Table 2). The content of the intervention was developed by adapting CTI with components of Cornerstone through a stakeholder feedback process that centered a young adult working group (YWG). The YWG led the development of a set of guiding values and provided feedback on the roles for each member of the *Charge Up!* team. Our primary partner agency that will collaborate on the first phase of the trial, was trained on the intervention prior to the start of the first phase of the trial. Prior to the start of phase 2 of the intervention, the TH/RRH case managers will be trained in the refined *Charge Up!* intervention. Two new roles will be added to support the case managers to provide enhanced mental health supports which are funded through the study. A mental health professional called a healing partner will assess, provide time limited mental health support, and ensure connection to mental health treatment when a young adult desires it. A transition support specialist (adapted from the recovery role model in Cornerstone Coordinated Community Care, C4) will also be part of the team. This will be a person with lived expertise of mental illness and housing instability who has been successful in achieving housing stability and successfully managing their mental health for at least a year. This role provides coaching and skill building activities and instills hope, providing a model of success. The intervention will run for 6 months, the time period proposed for CTI for RRH with adults, though case managers remain involved with young adults in a limited role as long as they are receiving RRH (average of 12 months).

**Table 2 Tab2:** Charge Up! intervention roles adapted from prior interventions

Core component	Lead personnel	Difference from current practice	Original intervention
Transitional case management based on CTI model	TH/RRH case manager	Training in CTI approach for current case managers	CTI C4 CTI elements
Mental health assessment and treatment connections	Healing partner	Currently referred out, now starts in the Charge Up program, with connection to longer term supports	C4 boundary spanning case manager
Mentoring and skill building	Transition support specialist	Currently no structured skill building activities or mentorship	C4 recovery role model

Treatment as usual will be assignment to one of the community agencies administering the TH/RRH program with housing and case management alone. Because TH/RRH is a developing program in our setting, we are prepared to carefully track TAU across multiple agencies. All TH/RRH programs currently provide the same housing support model, which provides time-limited assistance with housing and a housing case manager; however, the length of TH and RRH varies across agencies. Referral resources for mental health treatment will be provided at the point of intake for all that screen into the study but are randomized to TAU. We will assess the frequency of contacts with the case manager and other supports provided in TAU through structured items during interviews at 3, 6, and 12 months and include open-ended questions to describe supports provided.

### Feasibility and acceptability measures

To assess feasibility outcomes we will examine the constructs of acceptability, demand, practicality, and integration [48]. To assess demand, we will track how many YAEH are referred to the intervention, how many go through screening and express interest in the study, and how many are successfully enrolled. We will track how many sessions with intervention team members youth attend (in person or via zoom) at each phase of the intervention and our team will track retention of intervention and control condition participants at each measurement point, implementing strategies to increase retention if needed. Acceptability will be assessed through qualitative feedback about the intervention through open ended questions at each measurement point and as part of the final qualitative interview with participants and case managers. Practicality and integration will be assessed through qualitative interviews with case managers at the end of each phase of the study through questions about the challenges of coordinating with the larger team, the time involved in supporting the intervention, and its fit with the existing set of referral processes and resources available in the system.

### Proposed outcome measures

A summary of measures identified to assess proposed outcomes in the study is provided in Table 3. Measures of intervention targets used in prior studies of CTI with adults are included as well as measures used previously in C4 to assess stigma and hope. In addition, case managers will report on community connectedness, social support, and family relationships to provide additional data to triangulate and strengthen the self-report measures. The proposed measures will be assessed for acceptability based on length of the interview, participant response burden, and interviewer feedback following the first phase of the feasibility study and then used to explore reliability using Cronbach’s alpha following the randomized feasibility pilot.

**Table 3 Tab3:** Proposed outcome measures for Charge Up!

Construct	Instrument	Reliability/validity	Timing
Primary outcomes			
Housing stability	Housing Security Scale [50] Number of days homeless, Number of moves in prior 90 days	Alpha = 0.68; housing satisfaction subscale alpha = 0.74 [50]	Baseline, 3 months, 6 months, 12 months
Mental health			
Diagnosis of common disorders	MINI International Neuropsychiatric Interview Screen 7.0.2 [51, 52]	Kappa = 0.51–0.84 [48]	Baseline, 12 months
Depressive symptoms	Patient Health Questionnaire; PHQ-9 [53], 8 items	Alpha = 0.86–0.89 [53]	Baseline, 3 months, 6 months, 12 month
Anxiety symptoms	Generalized Anxiety Disorder; GAD-7 [54], 7 items	Alpha = 0.92 [54]	Baseline, 3 months, 6 months, 12 month
PTSD symptoms	Primary Care PTSD Screen (PC-PTSD) [55], 4 items	Test re-test = 0.83, Sensitivity = 0.78, Specificity = 0.87 [55]	Baseline, 3 months, 6 months, 12 months
Other mental health symptoms	Colorado Symptom Inventory [56], 14 items	Alpha = 0.77–0.85 [56]	Baseline, 3 months, 6 months, 12 months
Secondary outcomes			
Mental health service use/treatment engagement	Self-report of taking medication, attending appointments; casemanager report of appointment attendance Client Engagement in Child Protective Services Scale [57], modified for mental health services; 8 items	Strong face validity, used in prior studies Alpha = 0.91 [58]	Baseline, 3 months, 6 months, 12 months Baseline, 3 months, 6 months, 12 months
Hypothesized mediators (underlying mechanisms)			
Family relations	2 subscales Quality of Life Inventory, 3 items [59] Systematic Clinical Outcome Routine Evaluation Index of Family Functioning and Change [60] Case manager report	Alpha = 0.67–0.87 [59] Alpha = 0.90–0.93 [60]	Baseline, 3 months, 6 months, 12 months
Social support	MOS Support Scale, 15 items [61] Interpersonal Support Evaluation, 12 items [62] Case manager report	Alpha = 0.93 [61] Alpha = 0.91 [62]	Baseline, 3 months, 6 months, 12 months
Community connectedness	Community Integration Scale [63], 18 items Adult Personal Well Being Index Assessment Scale [65], 7 items Case manager report	Alpha = 0.75 [64] Item loadings = 0.51–0.72 [66]	Baseline, 3 months, 6 months, 12 months
Stigma	Stigma subscale, Inventory of Attitudes Toward Seeking Mental Health Services [67], 12 items	Alpha = 0.83 [68]	Baseline, 3 months, 6 months, 12 months
Hope	The Hope Scale [69], 12 items Life Orientation Test-Revised, 10 items [70]	Alpha = 0.71 Alpha = 0.78 [70]	Baseline, 3 months, 6 months, 12 months
Self-efficacy	Generalized Self-efficacy scale [71], 10 items Perceived Behavioral Control [73], 8 items	Alpha = 0.86–0.94 [72] Alpha = 0.60, 0.78	Baseline, 3 months, 6 months, 12 months

### Treatment fidelity

Treatment fidelity in the CTI intervention is assessed through the use of standardized documentation that tracks the phases and contacts for each participant [74]. We have adapted those forms for this study and will assess how well they work for *Charge Up!* and refine them through the first phase of the trial. We have identified guiding principles with our youth working group for the *Charge Up!* intervention (Grace, Authenticity, Accountability, Power Sharing, Systems Change and Culture of Care) and we will focus on incorporating questions into the documentation and/or developing new tools that operationalize these principles in action across activities. We will iteratively test and modify fidelity measures to create documentation to assess fidelity that will accompany the *Charge Up!* intervention at the end of this study.

### Data management and analysis

Qualitative data will be digitally recorded, then transcribed and stored on a secure data platform. Quantitative data will be collected using Qualtrics and stored on the secure data platform. Participant data will have a study participant number but no other identifying information and will be stored on the secure platform in a password protected file separate from identifying information. Structured interview data will be reviewed regularly by the study team for completeness and examined for missing values or outliers.

For the qualitative analysis focused on feasibility and acceptability of the *Charge Up*! intervention, we will analyze open-ended responses from participants at each survey administration and transcripts of interviews with participants and intervention staff using thematic content analyses [75]. A team of coders will develop a codebook through iterative discussions, then code interviews and examine common themes across the sample [76]. Preliminary results will be shared with participants (YAEH and staff) in a member checking process and compared with the quantitative results on the implementation outcomes measures. Intervention procedures and study measures will be modified based on feedback received in the first phase of the feasibility study for further testing and exploration in the randomized feasibility pilot in phase 2.

#### Progression criteria

Following the conclusion of the second phase pilot and feasibility trial, we will assess several criteria to determine whether the intervention and associated procedures are ready for progressing to a larger trial. These are presented in Table4 below in line with prior recommendations [77] to clearly delineate the key considerations that would indicate that the trial is not successful and procedures need to be reconsidered (STOP), criteria that would suggest the need to amend current procedures but proceed with the next phase (AMEND) and criteria that would indicate success without need for significant refinement (PROCEED).

**Table 4 Tab4:** Progression Criteria Following Phase 2 Trial

	STOP	AMEND	PROCEED
Recruitment	<50% of participants approached agree to randomization and are enrolled in the study	50–75% of participants approached agree to randomization and are enrolled in the study	>75% of participants recruited are enrolled
Intervention Delivery	<50% of the study participants randomized to the intervention are still receiving the intervention 3 months after enrollment	50–75% of the study participants randomized to the intervention are still receiving the intervention 3 months after enrollment	75% or more of study participants randomized to the intervention are still receiving the intervention 3 months after enrollment
Acceptability	More than half of staff and participants report problems with acceptability, minimal clear targets identified for improvement	Most participants and staff report intervention is acceptable and there are clear targets for improving staff and participant experience	Intervention participants and staff report intervention is acceptable to them
Study Retention	<50% of those enrolled in the study complete the 6 month follow up interview	50–70% of those enrolled in the study complete the 6 month follow up interview	70% or more of the study participants complete the 6 month follow up interview

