For the first phase of the open trial, we aim to recruit a sample of 8 young adults who are receiving TH/RRH services at our partner agency. During the second phase of the trial, we will expand recruitment to enroll 52 young adults with mental health history or symptoms and randomize half to each condition. Based on current housing capacity and our prior research, we estimate that 60–75% will screen positive for mental health problems as assessed with the Kessler-6 or prior history so at current capacity we would identify 4–6 participants per month that are eligible for the study and enroll 2–3 of these for approximately 12 months in the intervention condition and 2–3 participants per month for 12 months in the TAU condition.

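### Table 4's recruitment row switches numerator and denominator between columns and defines neither base, so one dataset can meet STOP or AMEND and PROCEED at once

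*Protocol article*

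**What the plan says.** Table 4 of the protocol article (Progression criteria) sorts the phase 2 pilot into STOP, AMEND or PROCEED on four rows. The recruitment row reads:

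- STOP: "<50% of participants approached agree to randomization and are enrolled in the study"
- AMEND: "50–75% of participants approached agree to randomization and are enrolled in the study"
- PROCEED: ">75% of participants recruited are enrolled"

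The article does not define *approached* or *recruited*. The counts it plans to keep use other labels. The Sample section lists wait-listed, contacted, enrolled and meeting criteria. The section on feasibility and acceptability measures lists referred, screened and interested, and enrolled.

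The order of events is described in two ways. In the Sample section, screening takes place during housing prioritization, and those who qualify are then told about the study. Eligibility determination and retention opens with screening followed by invitation. It then describes young adults hearing of the study at program intake and agreeing to have their names passed on, after which "The team will screen for eligibility and schedule a baseline interview".

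On screening yield, the Sample section says "we estimate that 60–75% will screen positive for mental health problems as assessed with the Kessler-6 or prior history" and that "we would identify 4–6 participants per month that are eligible for the study".

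**The concern.** The three cells look like one scale cut at 50% and 75%, but the top band measures something else. Its base moves from people approached to people recruited, which may be a smaller group further along the pathway, and its numerator no longer requires agreement to randomization. A low uptake among those approached can therefore sit beside a high fraction among those recruited, and the table does not say which governs.

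This matters because the sample-size section makes feasibility of recruitment and randomization, with retention, the main purpose of the pilot, and this row is the one that judges recruitment. If the base is chosen after the counts are known, the choice of base can choose the column.

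**Working it through.** **1. The plan's own accrual figure.** Inputs: 4–6 eligible per month, 2–3 enrolled per arm per month, 12 months (Sample).

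- Total: 4 × 12 = 48 to 6 × 12 = 72.
- Per arm: 2 × 12 = 24 to 3 × 12 = 36.
- The planned 52 (26 per arm, 52/12 = 4.33 per month) lies inside both ranges, so it is reproduced.

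The projection enrols as many per month (2–3 plus 2–3) as it identifies as eligible (4–6). It therefore assumes that nearly every eligible person accepts. The acceptance fraction is what this row has to test.

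**2. Can two columns be met together?** Fix enrolment at 52 and let the recruited be a subset of the approached.

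- STOP needs 52/approached < 50%, so 105 or more approached (52/105 = 49.5%).
- PROCEED needs 52/recruited > 75%, so 69 or fewer recruited (52/69 = 75.4%).

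These conditions do not exclude each other. With assumed counts, since the article gives none:

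| Approached | Recruited | Enrolled | Enrolled/approached | Enrolled/recruited |
|---|---|---|---|---|
| 120 | 60 | 52 | 43.3% (STOP) | 86.7% (PROCEED) |
| 90 | 60 | 52 | 57.8% (AMEND) | 86.7% (PROCEED) |

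With a single base the overlap disappears. At 52 enrolled, 105 or more in the base is STOP, 70–104 is AMEND (52/104 = 50.0%, 52/70 = 74.3%), and 69 or fewer is PROCEED.

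**3. Does it matter which single base is used?** Let *s* be the screen-positive fraction (0.60–0.75, Sample) and *c* the acceptance among eligible people (assumed). Counted after screening, the expected fraction is *c*. Counted before screening, it is *s* × *c*.

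| Acceptance *c* | Base after screening | Base before screening (*s* × *c*) |
|---|---|---|
| 100% | 100% (PROCEED) | 60–75% (AMEND) |
| 90% | 90% (PROCEED) | 54–67.5% (AMEND) |
| 80% | 80% (PROCEED) | 48–60% (STOP or AMEND) |

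The same acceptance falls in different columns according to the base.

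**4. Is PROCEED ruled out with a base before screening?** No. Exact binomial probability of observing more than 75%, that is at least 53 of 70 (70 is about 52/0.75):

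- *s* = 0.75: 0.51 at *c* = 100%, 0.09 at 90%, 0.004 at 80%.
- *s* = 0.60: 0.004 at *c* = 100%.

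The result is not expected, and in most of these scenarios it is unlikely, but it is possible.

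**The case against.** The best defence is that the last cell is shortened wording. The cut-points run along one scale, and the Study Retention row also rephrases its base between columns without apparently changing it. The natural reading is eligible people asked to join: agreeing to randomization is a question put to eligible people, the Sample section informs only those found eligible, the eligibility section opens with screening before invitation, and the accrual projection runs from eligible to enrolled. Recruitment is also one of four rows, with no rule that it decides alone, and the tracked counts would let the intended fraction be recovered.

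Much of this stands. It supports a base after screening, and it makes the defect cheap to repair. It does not remove the conflict: the printed cells differ in both parts of the fraction, the terms are undefined, and the later sentences of the eligibility section put screening after first contact.

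Three stronger readings are tempting and not supported:

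- **PROCEED is unreachable.** The 60–75% is a planning estimate, not a cap. The argument also needs a base before screening in the PROCEED cell, which the cell does not state and which the Sample section and the opening of the eligibility section do not support.
- **PROCEED is met automatically** because recruited people are enrolled by definition. The article gives no such definition.
- **The Acceptability row needs percentage bands.** That row is judged from open-ended responses and interviews by thematic analysis, so numerical bands would largely be a preference.

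**Conclusion.** The recruitment row is wrong as written. Numerator and denominator both change at the PROCEED column, and neither base is defined, so the row need not return one verdict from one dataset. The illustrative split, 43.3% against 86.7%, rests on assumed counts and on the recruited being a subset of the approached. It shows that the conflict can occur, not how likely it is.

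The choice of base is a real decision: the plan's 60–75% estimate puts the expected fraction before screening at no more than 60–75% under full acceptance, against up to 100% after screening. This goes no further than saying that PROCEED is not expected with a base before screening.

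**What to change.** Use one fraction in all three recruitment cells: young adults enrolled and randomized, divided by young adults who screened eligible and were offered the study. Keep the existing cut-points: STOP below 50%, AMEND 50–75%, PROCEED above 75%. Report screening yield (eligible divided by screened) separately, so that a low prevalence of eligibility is not read as refusal. Reconcile the Sample and Eligibility determination and retention sections on whether screening comes before or after the young adult is told of the study.

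The cost is wording. The contact, screening, eligibility, interest and enrolment counts are already to be tracked; the log only needs to mark which eligible people were offered the study. Make the change before the phase 2 recruitment counts are judged.
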